### Hypotheses for the primary outcome: physical activity

*Hypothesis 1A*: White participants will report engaging in more physical activity than participants from minority groups at baseline (i.e., a significant main effect of race/ethnicity).
*Hypothesis 1B*: There will be a greater increase in physical activity from baseline among the intervention groups than among the control groups (i.e., a significant main effect of condition).
*Hypothesis 1C*: There will be a greater increase in physical activity from baseline for minority participants in the intervention groups than White participants in the intervention groups (i.e., a significant race/ethnicity by condition interaction).
*Hypothesis 1D*: Participants in the intervention groups will experience a greater increase in need fulfillment during exercise (i.e., autonomy, competence, relatedness and intrinsic motivation) which will mediate the effect on physical activity.$$ Condition\to Need\  Fulfillment\to Physical\  Activity $$

*Hypothesis 1E*: Participants in the intervention condition will report that their instructor utilizes MI skills more frequently which will mediate the effect on physical activity.$$ Condition\to Instructor\hbox{'}s\  Perceived\  use\  of\ MI\  Skills\to Physical\  Activity $$

### Hypotheses for secondary outcomes: need fulfillment, well-being, adherence

*Hypothesis 2A*. Participants in the intervention groups will experience a greater increase in need fulfillment, psychological well-being, and physical activity adherence than participants in the control groups (i.e., a significant main effect of condition).

## Methods/Design

The study has been approved by Syracuse University Institutional Review Board. The intervention is based on one motivational theory, SDT, and a clinical approach, MI, as well as fitness recommendations from the CDC (i.e., 150 min/week of moderate intensity or 75 min/week of vigorous intensity aerobic activity and muscle-strengthening exercises). The study will be conducted at two Syracuse-based YMCA facilities (i.e., the Downtown and Southwest YMCAs). These facilities were chosen because there is variability in the racial/ethnic composition of the clients in these locations. Due to the racial/ethnic composition of the staff at these YMCAs, all of the exercise instructors in this study will be White.

### Participants

An a priori ANOVA power analysis was conducted to determine how large a sample would be needed to detect significant main effects and interactions (G*Power version 3.1.3., 2010). This was estimated using a large effect size (f = 0.50), an alpha level of 0.05, and the power was estimated at 0.80. This power analysis determined that 48 participants are needed in the sample in order to detect a statistically significant change in an effect of this size.

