#### Assignment to condition

The current study is a parallel group, two arm, superiority trial with 1:1 allocation ratio. First, participants were allowed to choose whether they wanted to attend the Downtown YMCA or Southwest YMCA. Next, stratified randomization was employed such that participants were separated by race/ethnicity (i.e., minority versus non-minority) and participants were randomly assigned to the control or intervention condition within each site. A computer-generated allocation sequence was used and assignment to condition was made using sequentially numbered, opaque, sealed envelopes. Throughout the study, participants and the research assistant (i.e., an outcome assessor) will remain blind to condition. Due to the nature of the study, the exercise instructors and the experimenter (i.e., an outcome assessor and data analyst) will not be blind to condition.

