### Planned statistical analyses

The analysis plan involves a 2 (race/ethnicity) × 2 (condition: intervention vs. control) factorial ANCOVA with pretest scores entered as covariates to test Hypotheses 1A-1C involving physical activity (assessed by the International Physical Activity Questionnaire [63]). Analysis of variance will be used to test Hypothesis 2A involving need fulfillment (assessed by the Basic Psychological Needs in Exercise Scale [65] and the Behavioural Regulation in Exercise Questionnaire [66]), physical activity adherence (assessed by how often participants attend the YMCA six months post-intervention), and psychological well-being (assessed by the Psychological General Well-being Index [64]). When examining whether mediators account for the relationship between intervention condition and physical activity, the Preacher and Hayes [69] nonparametric bootstrap approach will be used (i.e., Hypothesis 1D using the Basic Psychological Needs in Exercise Scale [65] and the Behavioural Regulation in Exercise Questionnaire [66] and Hypothesis 1E assessed by the Client Evaluation of Motivational Interviewing Scale [60]).

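### The stated 48 participants does not belong to the 1-df main effects and interaction it is said to cover, and the text does not say that f = 0.50 means a 2 SD difference in effects for Hypothesis 1C

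*Protocol article*

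**What the plan says.** The Participants section describes an a priori ANOVA power analysis run "to determine how large a sample would be needed to detect significant main effects and interactions". The inputs are Cohen's f = 0.50, which the text labels large, with "an alpha level of 0.05, and the power was estimated at 0.80". The result is given as "This power analysis determined that 48 participants are needed in the sample", and the claim is limited to an effect of that size. Neither the numerator df nor the number of groups is given. No SD, raw difference or source is offered for f.

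Planned statistical analyses specifies a "2 (race/ethnicity) × 2 (condition: intervention vs. control) factorial ANCOVA with pretest scores entered as covariates" for Hypotheses 1A to 1C. The hypotheses section ties 1A and 1B to main effects and 1C to "a significant race/ethnicity by condition interaction". Assignment to condition describes a "parallel group, two arm, superiority trial with 1:1 allocation ratio". Participants enrolled and Table 1 report 57 people: 27 intervention and 30 control.

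**The concern.** There are two separate points.

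First, a 2 × 2 design has two main effects and one interaction, each with a single numerator df. If the calculation is for those effects, it should be a 1-df calculation. If 48 comes from another test, the stated pairing of 48 participants with 80% power is wrong for every test the plan names.

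Second, one value of f is applied to main effects and interaction alike. The same f stands for very different raw contrasts in the two cases, and the article does not say so. This matters most for 1C. The abstract singles out the larger expected gain in minorities, and the Discussion says the study will determine whether such interventions can reduce the disparity. A reader who sees one sample size covering interactions may take a non-significant 1C as evidence of no differential effect.

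**Working it through.** **Inputs.** f = 0.50, alpha 0.05, power 0.80 and stated N = 48 (Participants). Four cells and a pretest covariate (Planned statistical analyses). Enrolled cells from Table 1: White 15 intervention and 16 control; minority 9 + 3 + 0 = 12 intervention and 11 + 1 + 2 = 14 control.

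**Method.** Noncentral F with λ = f² × N and denominator df = N − groups (− 1 with a covariate), taking the smallest N with power of at least 0.80.

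**Step 1: reproduce 48.**

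| Numerator df | Groups | Smallest N | Power at that N |
|---|---|---|---|
| 3 | 4 | 48 | 0.803 (0.802 with one covariate) |
| 2 | 4 | 42 | 0.803 |
| 1 | 4 | 34 (36 for equal cells) | 0.805 |
| 1 | 2 | 34 | 0.807 |

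Of the settings tried, only 3 df with four groups gives exactly 48. There are two near misses at 49: 3 df with eight groups, and 34 inflated for 30% dropout (34 / 0.70 = 48.6, rounded up). Each needs an input that the power paragraph does not state. With f = 0.40 and 1 df the answer is 52.

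**Step 2: power of the named tests at f = 0.50.** For a 1-df effect in four cells, λ = 0.25 × 34 = 8.5 gives power 0.805. At N = 48, λ = 0.25 × 48 = 12 gives 0.923. At N = 57, λ = 0.25 × 57 = 14.25 gives 0.960.

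**Step 3: what f = 0.50 means** (balanced 2 × 2, σ = within-cell residual SD).
- Main effect: the two margins lie at ±δ/2, so f = δ/(2σ) and δ = 2 × 0.50 = 1.0σ.
- Interaction: the cell deviations are ±γ and the difference between the two intervention effects is 4γ. So f = γ/σ, and the difference is 4 × 0.50 = 2.0σ.

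**Step 4: detectable effects.** The smallest f with 80% power for a 1-df test is 0.413 at N = 48 and 0.378 at N = 57.
- N = 48: 2 × 0.413 = 0.83σ for a main effect; 4 × 0.413 = 1.65σ for the interaction.
- N = 57: 2 × 0.378 = 0.76σ for a main effect; 4 × 0.378 = 1.51σ for the interaction.

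**Step 5: enrolled cells.** The SE of the difference between intervention effects is √(1/15 + 1/16 + 1/12 + 1/14) = √0.2839 = 0.533σ, with 57 − 5 = 52 denominator df.

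| True difference between intervention effects (residual SD) | Power for 1C |
|---|---|
| 0.5 | 0.15 |
| 0.8 | 0.31 |
| 1.0 | 0.45 |
| 1.52 | 0.80 |
| 2.0 | 0.96 |

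For the condition effect averaged equally over the two race strata, the SE is half as large (0.533 / 2 = 0.266σ). The difference needed for 80% power is therefore 1.52 / 2 = 0.76σ, and power at 0.5σ is about 45%.

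The effect sizes in this table are illustrative, since the article gives no SD. All figures assume independent participants and no loss to follow-up.

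**The case against.** The strongest reply is that nothing claimed for the trial is overstated at the stated effect size. The article limits its claim to an effect of f = 0.50. At that size 48 participants give 92% power for a 1-df test, the enrolled 57 exceed both 48 and 34, and correcting the df alone would lower the requirement. This stands. A reader might infer that the df slip left the trial too small for its own assumption; the arithmetic shows the reverse.

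A reader might also infer that the df choice conceals weak power for 1C. It does not. That weakness comes from f = 0.50, which the article states openly and calls large. A correct 1-df calculation at f = 0.50 would leave the 2 SD requirement equally unexplained.

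It is also tempting to call that requirement implausible, or to say the trial lacks power for any realistic interaction. The article gives no SD, expected IPAQ difference or prior interaction estimate, so neither can be shown. The units matter here too. These are residual SDs after pretest adjustment. If the pre-post correlation were 0.3 to 0.7 (an assumption), 1.52 residual SD would be 1.52 × √(1 − 0.3²) = 1.45 to 1.52 × √(1 − 0.7²) = 1.09 raw SD. That is smaller, but still large.

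Lastly, the 3-df setting is inferred from an exact match. The mismatch does not depend on that inference: the stated inputs and named effects give 34, whatever produced 48.

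**Conclusion.** The point holds in two limited parts.

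1. The sample size and power quoted do not belong to the tests named. The 1-df answer is 34 (36 for equal cells), and 48 corresponds to about 0.92 power rather than 0.80. The error is on the safe side at f = 0.50.
2. The article applies one f to 1B and 1C without saying that it means 1.0 residual SD for one and 2.0 for the other, and without justifying either. At the enrolled sample, 1C reaches 80% power only at about 1.5 residual SD and would miss a true difference of 1.0 residual SD slightly more often than not (power 0.45).

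These results rest on a 1-df test at alpha 0.05, independent observations and complete data. Delivery in group classes and any loss would be expected to reduce power, by an amount the article gives no basis to calculate. The article sets no rule for interpreting a null 1C, so misreading it is a risk to guard against and not something the plan commits to.

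**What to change.** Keep the a priori calculation as the record of how the size was set; overwriting it with figures computed after enrolment would misreport that history. Then:

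- State the numerator df and number of groups that produced 48.
- Add that the named 1-df effects need 34 at f = 0.50, and that 48 gives about 0.92 power for each.
- Say what f = 0.50 means for 1B (1.0 residual SD) and for 1C (2.0 residual SD between the two intervention effects), and give the basis for it or say there is none.
- Give the effects detectable with 80% power at the enrolled 57: about 0.76 residual SD for condition and about 1.5 for race/ethnicity by condition, before class clustering and loss.
- State that 1C is powered only for a very large difference in effects, and that a non-significant result will be reported with its confidence interval and not read as showing no differential effect.

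The cost is text only. No participants, visits or analyses are added. The stated capability for main effects at f = 0.50 improves, while that for 1C becomes more modest.

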#### Participants recruited

Participants were recruited using online advertisements (YMCA Facebook website) and hard-copy advertisements that were displayed at the YMCA and throughout the city of Syracuse at public libraries, community centers, churches, etc. If the YMCA members were interested in participating, they completed a survey online through Qualtrics or a hard copy version of the survey in order to determine whether they were eligible to participate in the study. The inclusion criteria mandated that participants were currently healthy enough to exercise once a week, not be pregnant or planning to get pregnant within the next 3 months, were willing to attend an exercise class once a week for 12 weeks, were willing to complete questionnaires at baseline and 12 weeks, allowed the intervention staff to monitor their attendance at the YMCA for 6 months post intervention, and allowed the exercise instructor to create an audio recording of all of the intervention sessions.

#### Participants enrolled

Although 128 individuals completed the recruitment survey to enroll in the study, 33 did not meet the eligibility requirements, 10 did not attend any of the exercise classes, and 28 dropped out of the study because the YMCA director changed the time of an intervention class and control class at one site from an evening class to a morning class (see Fig. 1). In total, 57 participants enrolled, were randomized into the intervention or control condition, and attended the first exercise class. The experimenter obtained written informed consent from all participants before they participated in the study. Table 1 contains demographic information about the participants who attended this physical activity intervention. Participants’ age, education, racial/ethnic group, and sex did not significantly differ by condition (i.e., intervention or control).

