### Measures

Participants will complete a number of surveys during pre-intervention, session 4, session 8, and session 12. All of the data will be collected, entered into the computer, and maintained by the experimenter. A description of the primary and secondary outcome measures are listed below, as well as the measures used to assess treatment fidelity.

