### Primary outcome measures

#### Physical activity

Physical activity will be assessed using the YMCA’s records of how often the participant came to the control or intervention class (as a measure of persistence), how often the participant attends the YMCA during the intervention and 6 months following the intervention (as a measure of adherence post-intervention). Physical activity will also be assessed using two self-report measures: one question to assess muscle-strengthening exercise from the Behavioral Risk Factor Surveillance System Questionnaire [62], as well as using the long and short version of the International Physical Activity Questionnaire (IPAQ) [63]. The IPAQ weights the frequency of strenuous, moderate and low intensity physical activity by its metabolic equivalent, which quantifies the energy expenditure in each level of physical activity based on its intensity.

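### Week-12 questionnaires are scheduled in class at session 12, so the IPAQ comparison, followed as written, is between people still attending, a group selected after randomisation

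*Protocol article*

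**What the plan says.** All places are in the protocol article.

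- **Collection.** Measures: "Participants will complete a number of surveys during pre-intervention, session 4, session 8, and session 12". Table 2 ticks the pre- and post-test survey at sessions 1 and 12. Its footnote puts the consent form in that same survey. No other way of reaching absentees at week 12 is described.
- **Attendance as an outcome.** Under Primary outcome measures, Physical activity, YMCA records are to show "how often the participant came to the control or intervention class (as a measure of persistence" (the bracket closes after the quoted words). Hypothesis 2A predicts a greater increase in adherence in the intervention groups.
- **Analysis.** Planned statistical analyses specifies a 2 × 2 ANCOVA (race/ethnicity by condition) on IPAQ physical activity with pretest scores as covariates. It therefore needs a post-test IPAQ score for everyone analysed.
- **Sample.** Participants enrolled: "57 participants enrolled, were randomized into the intervention or control condition, and attended the first exercise class". The same section reports that "10 did not attend any of the exercise classes, and 28 dropped out of the study because the YMCA director changed the time" of two classes at one site.
- **Size.** Participants: "This power analysis determined that 48 participants are needed in the sample", with "an alpha level of 0.05" and f = 0.50; "the power was estimated at 0.80".

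**The concern.** A randomised comparison is protected only while the people compared are those who were randomised. If the post-test score exists only for people present at session 12, inclusion in the primary analysis depends on behaviour after randomisation. Here that behaviour is one the trial expects to differ by arm.

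The direction of the bias depends on whom the intervention retains. Suppose it keeps less active people in class who would have left the control class. The intervention mean is then pulled down relative to a more selected control group, and the effect is understated. If it drives such people away, the effect is overstated. The result alone would not show which had happened.

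The other questionnaire outcomes (well-being, need fulfilment, motivation) depend on session 12 in the same way. Outcomes taken from YMCA attendance records do not.

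**Working it through.** **1. The plan's own figures.** Flow: 128 − 33 = 95 eligible; 95 − 10 − 28 = 57, as stated. Sample size: noncentral F with noncentrality N·f², f = 0.50, alpha 0.05. With 3 numerator degrees of freedom and 4 cells, the smallest N giving power 0.80 is 48 (power 0.803; 0.802 with one covariate). Both figures reproduce.

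**2. Room for loss.** 57 − 48 = 9, and 9/57 = 15.8%. Losing 10 (10/57 = 17.5%) leaves 47, below the stated requirement. This concerns power only. A single 1-df effect of f = 0.50 needs N = 34 under the same method, so the shortfall would be against the plan's own figure and would not ruin the 1-df tests.

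**3. Bias, simple form.** Let non-attenders be δ SD less active than attenders in the same arm, with no treatment effect, and let a fraction m of the arm miss session 12. The attenders' mean exceeds the full arm mean by m·δ, so the bias in the arm difference is δ·(m_intervention − m_control). Assumed inputs, not in the documents: δ = 0.5, m = 0.10 in the intervention arm and 0.30 in control. Inflation is 0.05 and 0.15 SD, so the bias is 0.5 × (0.10 − 0.30) = −0.10 SD, against the intervention.

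**4. Bias, selection model.** Let session 12 attendance be a threshold on a latent propensity that has correlation ρ with the outcome. With a proportion p attending and t = Φ⁻¹(1 − p), the attenders' mean is shifted by ρ·φ(t)/p. The bias is the difference of this shift between arms. For p = 0.8 the factor φ(t)/p is 0.350, for 0.6 it is 0.644, and for 0.9 it is 0.195. Assumed attendance is intervention versus control, with no true effect:

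| Attendance | ρ = 0.2 | ρ = 0.3 | ρ = 0.5 |
|---|---|---|---|
| 80% v 80% | 0.00 | 0.00 | 0.00 |
| 80% v 70% | −0.03 | −0.04 | −0.07 |
| 80% v 60% | −0.06 | −0.09 | −0.15 |
| 90% v 60% | −0.09 | −0.14 | −0.22 |

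Swapping the arms reverses the sign. The pretest covariate removes the part of selection that baseline activity explains. To apply the table to the ANCOVA, read ρ as the correlation that remains after the pretest, and the SD as the residual SD.

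**5. Scale.** For two equal groups f = 0.50 is d = 2 × 0.50 = 1.0. The unadjusted standard error of the arm difference with 27 and 30 is √(1/27 + 1/30) = 0.27 SD. A bias of 0.05 to 0.2 SD is thus 5% to 20% of the planned effect, and at most about three quarters of that standard error (0.2/0.27 = 0.74).

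**The case against.** The strongest reply is that the article does not say absentees go unmeasured. An inclusion criterion requires willingness to complete questionnaires at baseline and at 12 weeks, which is a commitment in time and not tied to attending. Missing-data methods and analysis sets may stand in a fuller plan that is not shown, and the article does not call its analysis complete-case. The IPAQ is not named in Table 2's footnote for the post-test survey, so its week-12 timing has to be read from the Measures and analysis sections. All of this stands, and for that reason the point is limited to the collection schedule, which the article does fix. Methods for missing data cannot fully replace outcomes that were never collected.

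It is also fair that the size of the bias rests on assumed inputs, that the pretest covariate reduces it, and that it is small beside the planned effect.

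A reader might infer something stronger: that 38 of 95 (40%) were lost after randomisation and that this loss shows the same bias. The documents do not support that, for four reasons.

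- Attendance at the first class precedes delivery of the intervention, and participants are described as blind to condition, so the intervention is unlikely to have changed it.
- The class-time change was an outside decision that moved a class in each arm.
- Participants chose a site before being randomised, so the 28 could have withdrawn before allocation.
- The flow diagram (Fig. 1) is not shown here.

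The excluded share of those randomised could therefore be 0 of 57, 10 of 67 (14.9%) or as much as 38 of 95. Since the consent form sits in the session 1 survey, those randomised and consented may be exactly the 57.

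**Conclusion.** The concern holds for session 12. As written, the post-test questionnaires reach only people still attending, and attendance is an outcome expected to favour one arm. The ANCOVA on IPAQ would then compare groups selected after randomisation.

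The bias is roughly 0.05 to 0.2 SD if attendance differs by some 20 to 30 percentage points and is moderately related to activity after allowing for the pretest. It is nil if attendance and selection are the same in both arms. None of these inputs is in the documents, and the sign could go either way. Separately, a loss of 10 or more of the 57 breaches the plan's own 48.

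The 40% is a share of eligible people. It is not shown to be loss after randomisation and should not be cited as the size of this problem.

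**What to change.** 1. State that the week-12 IPAQ and post-test survey go to every randomised, consented participant at 12 weeks, whether or not they attend session 12. Qualtrics and paper forms were both used for the eligibility survey and would serve.
2. State that all of these participants are analysed in the arm to which they were allocated.
3. If any of the 10 non-attenders or the 28 lost to the class-time change had already been allocated, say so and describe the comparison as one among people who attended the first class. If Fig. 1 already gives these counts, a sentence pointing to it is enough.

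The cost is a survey link or mailed form, some reminders and a few sentences of text. The drawback is that some participants answer in a different mode from those surveyed in class. Recording the mode would let this be examined. The article describes the surveys in the future tense, so on its own terms the change can still be made.
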